## Methods/design

### Study design

ARTEMISIA is a randomised, double-blind, placebo-controlled, parallel-group, exploratory, phase 2 study (NCT06435273). It aims to assess the effect of londamocitinib, administered twice daily via dry-powder inhalation for four weeks, on the wide spectrum of inflammatory signalling pathways that drive pathology in adults with moderate-to-severe asthma. The ARTEMISIA study is currently ongoing across 5 countries (Canada, Denmark, Germany, Spain, and the United Kingdom [UK]) and aims to enrol 48 participants, randomised 2:1 to londamocitinib or placebo respectively (see Fig. 2). Participants will be stratified based on fractional exhaled nitric oxide (FeNO) (≥ or < 25 parts per billion [ppb]); with at least 40% of randomised participants with FeNO ≥ 25 ppb and at least 40% with FeNO < 25 ppb at baseline.

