### Statistical considerations

All statistical analyses of primary, secondary and exploratory outcomes will be performed after database lock, which will occur after the last subject last visit study milestone.

Data on patient demographics and disease characteristics, as well as safety findings, will be reported descriptively for the full analysis set (all randomised participants who receive at least one dose of study drug irrespective of protocol adherence and continued participation in the study).

Due to the exploratory nature of the study, no formal power calculation was performed. The sample size of 48 participants was estimated based on a large sample z-statistic around the difference in change from baseline values between londamocitinib and placebo on the logarithmic scale. A pooled standard deviation for change from baseline across T2 genes was derived from a historical bronchoscopy study [13]. Assuming comparable variability, the estimated sample size will ensure that the two-sided 95% confidence intervals for the biomarkers of interest will not be wider than 0.72 on the log-change from baseline scale, which is considered sufficiently narrow for the purposes of this study.

The bulk RNA-sequencing data collected for the primary endpoint will be analysed using negative-binomial regression models designed for count-based gene expression data [16, 17]. Variations in sequencing depth between samples will be modelled, along with adjustment for study drug as a covariate. A natural-logarithm link function will be used for the generalised linear model, but results will be presented in terms of a log-2-fold change. The treatment effect on gene-expression change from baseline will be analysed in a paired fashion.

The secondary endpoints aim to evaluate the effect of londamocitinib compared to placebo on various bronchial biopsy measures throughout the study and will be analysed using analysis of covariance (ANCOVA) models. The within-participant change from baseline to end of treatment measures of STAT phosphorylation and airway inflammatory cells from the bronchial biopsies will be modelled individually on the log-scale and will include baseline value and study drug as covariates.

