Performing studies with complex sampling methods at scale increases the risk of logistical challenges and variation in sample collection and quality which may lead to a lack of veracity of the data that is collected. Given the risks and complexity, to perform bronchoscopy on participants at a scale which would allow the data collected to be related directly to clinical outcomes would be resource intensive and difficult to deliver. Identifying a relationship between central and peripheral biomarkers which can then be related to clinical outcomes in a separate large-scale study offers a solution to this problem. Evaluating epithelial gene signatures has allowed us to keep the sample size small, reducing possible site-to-site sampling variability and logistical complexity. By collecting the same peripheral samples in both the ARTEMISIA and AJAX studies, associations between biomarkers in central and peripheral samples will be evaluated, and subsequently related to clinical outcomes, without needing to expose large numbers of participants to the risks associated with invasive sampling.

Randomisation in the ARTEMISIA study will be stratified based on baseline FeNO as a non-invasive approach to enrol participants across the spectrum of T2- and T17-driven airway inflammation. FeNO level has previously been reported to be positively correlated with T2 gene expression signatures and inversely correlated with T17 gene expression in airway epithelial cells [13].

Key barriers to performing studies of this nature include participant acceptability but also feasibility of delivery at the site level. To address these challenges, the study protocol was reviewed and critiqued by a group of asthma patients, as well as a group of research nurses from the UK NIHR Clinical Research Facility Network. The study was also reviewed and subsequently adopted by the NIHR translational research collaboration. By incorporating the perspective of participants and research delivery staff, the authors hope to have created a study design which achieves its objectives but remains acceptable and feasible to deliver from the outset.

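### Randomisation is stratified by FeNO, but the stated primary and secondary models do not name the stratum; the only possible loss is precision, and it may be nil

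*Protocol article*

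**What the plan says.** Two parts of the protocol article bear on this.

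- **Design.** The Discussion states: "Randomisation in the ARTEMISIA study will be stratified based on baseline FeNO". Study design gives the cut at 25 ppb and a floor for each stratum, "with at least 40% of randomised participants with FeNO ≥ 25 ppb and at least 40% with FeNO < 25 ppb at baseline". The trial "aims to enrol 48 participants, randomised 2:1 to londamocitinib or placebo respectively", that is 32 and 16.
- **Analysis.** Statistical considerations describes the primary count model as follows: "Variations in sequencing depth between samples will be modelled, along with adjustment for study drug as a covariate". It adds: "The treatment effect on gene-expression change from baseline will be analysed in a paired fashion". The secondary models for STAT phosphorylation and airway cells are ANCOVAs of log-scale change that "will include baseline value and study drug as covariates".

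The FeNO stratum appears in neither description, and nowhere else does the article say that it enters a model. On the link between FeNO and the endpoint, the Discussion offers this: "FeNO level has previously been reported to be positively correlated with T2 gene expression signatures", with an inverse correlation for T17 expression.

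**The concern.** The usual principle is that a factor used to stratify randomisation also enters the analysis. Stratification balances the factor across arms, so the treatment estimate already varies less than under simple randomisation. A model that omits the factor leaves the between-stratum variance in its error term and does not see that gain. Its standard error then exceeds the true one, intervals are too wide and tests too conservative.

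This matters here because precision is the only stated basis for the sample size, and each participant undergoes two bronchoscopies. FeNO was also chosen because it is thought to track the T2/T17 axis that the primary endpoint reports on. The article names covariates for both types of model, so the mismatch with the randomisation is in what is stated, and does not rest on a detail left to a fuller plan.

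**Working it through.** **1. The article's own figure.** With a large-sample z interval, width = 2 × 1.96 × SD × √(1/32 + 1/16), and √(1/32 + 1/16) = 0.306. The article does not print the SD, so 0.72 cannot be reproduced independently. Solving for it gives SD = 0.72 / (2 × 1.96 × 0.306) = 0.60, taking 0.72 as the full width (1.20 if it were the half-width). N = 48 and 0.72 are compatible at SD 0.60. No FeNO term enters this calculation.

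**2. What adjustment could gain.** If the stratum explains a share R² of the variance of change, width becomes 0.72 × √(1 − R²), and the equivalent gain in participants is 1/(1 − R²) − 1. The article gives no R², so these values are assumptions. With strata of equal size, R² = 0.25d²/(1 + 0.25d²), where d is the between-stratum difference in change in within-stratum SDs; hence d = 2√(R²/(1 − R²)).

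| R² (assumed) | d needed | Width, T2 genes | Equivalent extra N |
|---|---|---|---|
| 0% | 0 | 0.72 | 0% |
| 5% | 0.46 | 0.70 | 5% |
| 10% | 0.67 | 0.68 | 11% |
| 20% | 1.0 | 0.64 | 25% |

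A 40:60 split changes the factor 0.25 only to 0.4 × 0.6 = 0.24.

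**3. What omission does to the standard error.** A simulation used 6,000 runs per scenario, no treatment effect, strata of 24 and 24, permuted blocks of three at 2:1, pre/post correlation 0.5, and normal log-scale data with within-stratum SD 1 standing in for the count model. FeNO shifts the expression level, the change, or both, in SD units. "SE" is the mean model standard error; "true" is the empirical SD of the estimate.

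| Model | Level shift | Change shift | Without stratum: SE / true (ratio) | Type I | With stratum: SE | Type I |
|---|---|---|---|---|---|---|
| Paired | 1 | 0 | 0.304 / 0.305 (1.00) | 4.7% | 0.304 | 4.7% |
| Paired | 1 | 0.3 | 0.308 / 0.306 (1.01) | 4.8% | 0.304 | 5.2% |
| Paired | 1 | 0.5 | 0.314 / 0.306 (1.03) | 4.2% | 0.305 | 5.0% |
| Paired | 1 | 1 | 0.342 / 0.308 (1.11) | 2.5% | 0.304 | 4.9% |
| Paired | 0 | 0.5 | 0.314 / 0.310 (1.01) | 4.8% | 0.304 | 5.4% |
| ANCOVA | 1 | 0 | 0.275 / 0.271 (1.01) | 4.7% | 0.267 | 5.2% |
| ANCOVA | 1 | 0.3 | 0.289 / 0.270 (1.07) | 3.5% | 0.267 | 4.6% |
| ANCOVA | 1 | 0.5 | 0.301 / 0.280 (1.07) | 3.3% | 0.267 | 5.1% |
| ANCOVA | 1 | 1 | 0.339 / 0.285 (1.19) | 2.0% | 0.266 | 4.7% |
| ANCOVA | 0 | 0.5 | 0.277 / 0.265 (1.05) | 3.9% | 0.266 | 4.5% |

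The empirical SDs carry Monte Carlo error of about 1/√(2 × 6,000) = 0.9%, so a ratio of 1.01 is barely distinguishable from 1. For the paired model, theory gives √(1 + 0.25d²): 1.03 at d = 0.5 and 1.12 at d = 1, in reasonable agreement with the table.

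**4. Which rows the article supports.** Its only evidence is a correlation with expression level for T2 and T17 genes. That corresponds to the rows with change shift 0: pairing removes a pure level effect, and the ANCOVA baseline term absorbs most of it.

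**5. Cost of the term.** With 48 complete pairs, the ANCOVA falls from 45 to 44 residual degrees of freedom. The t critical value moves from 2.014 to 2.015, under 0.1% of the interval width.

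**The case against.** The strongest reply is that the covariate descriptions need not be complete. For the primary model this is fair: a paired analysis needs participant and visit terms, and the sentence naming sequencing depth and study drug lists neither, so it cannot be exhaustive. A fuller plan, not shown, may contain the stratum. The reply is weaker for the ANCOVA, whose covariates are named plainly. In either case the published description and the randomisation should be brought into line.

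A second reply is that little is at stake. The trial is exploratory and hypothesis-generating, has no formal power calculation, and declares 0.72 narrow enough without any FeNO adjustment. The Discussion presents stratification as a way to enrol across the inflammatory spectrum, not as variance reduction. All of this stands and limits the weight of the point.

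A reader might also infer that FeNO is a known prognostic factor for the endpoints, so that the standard errors are certainly too large. The article does not support this. The endpoints are changes from baseline, and the cited correlation concerns expression level in T2 and T17 genes. Nothing is given for change, for the other gene sets, for STAT phosphorylation or for cell counts.

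Nor does it help to argue that high-FeNO participants have more T2 expression to suppress. That describes a drug effect differing by stratum, which a stratum term without a drug×stratum interaction captures only in part.

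**Conclusion.** The point holds as a mismatch between randomisation and stated analysis, with a conditional consequence. Neither model, as described, includes the factor on which participants are randomised.

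Omitting it causes no bias and no inflation of type I error. Where it matters, the error is conservative: from nil (paired primary analysis) or 1–2% (ANCOVA) if FeNO relates only to level, up to about 11% and 19% if it also shifts the change by 1 SD. The documents give nothing that places the trial within that range, and zero belongs in it.

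The interval widths of 0.72 down to 0.64 apply to T2 genes only, since the 0.72 rests on an SD for those genes; they do not carry over to the biopsy endpoints. The figures assume an SD of 0.60 (back-solved), pre/post correlation of 0.5, near-equal strata, complete pairs, and a normal model in place of the negative-binomial one. The omission and the direction of its effect are well supported; the size is not known.

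**What to change.** - **Secondary ANCOVAs:** add FeNO stratum (≥25 / <25 ppb, as randomised) as a fixed factor beside baseline value and study drug.
- **Primary paired count model:** specify participant, visit, visit×study drug and visit×FeNO stratum, and test visit×study drug. The stratum main effect is absorbed by the participant terms, so the interaction with visit is the term that is needed.
- If the stratum is left out on purpose, say so with the reason. If a fuller analysis plan already includes it, align the published description.

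The cost is one model term and about one degree of freedom per model, with no change to recruitment, sampling or randomisation. With the stratum in the model, simulated type I error stayed between 4.5% and 5.4% in every scenario.

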## Discussion

In the Phase 1 study (NCT04769869), inhaled londamocitinib was shown to have acceptable safety and tolerability, whilst also demonstrating the ability to significantly reduce FeNO in those with mild asthma [7]. This study provided evidence of inhibition of T2 inflammatory pathways in the absence of systemic target engagement by londamocitinib. The phase 2 ARTEMISIA study is designed to provide evidence of JAK1 target engagement directly in the lung, assess impact of londamocitnib on non-T2 inflammatory pathways, and explore additional molecular and cellular changes observed in the lung. In addition, this study will assess how those changes are reflected in peripheral samples from the nose, blood and urine.

The primary objective of ARTEMISIA is to assess the change in epithelial gene signatures of central airways following 4 weeks of exposure to londamocitinib. Many studies investigating the impact of drugs on the airways have focussed on the histopathological changes seen in the airway [18, 19]. Local effects of blocking IL-13 signalling on eosinophilic airway inflammation in moderate-severe asthmatics was investigated in the MESOS and CLAVIER studies [19, 20]. In these studies, neither tralokinumab nor lebrikizumab treatment resulted in a significant effect on change from baseline in airway submucosal eosinophils versus placebo. It should be noted however that enrolment to the CLAVIER study was stopped before inclusion of the planned number of participants. Inhibition of TSLP signalling in the CASCADE study did result in a significantly greater change from baseline to the end of treatment in airway submucosal eosinophils with tezepelumab compared to placebo (ratio of geometric least-squares means 0·15 [95% CI 0·05–0·41]; nominal *p* < 0·0010) [18]. To adequately assess these changes requires prolonged exposure to the drug and substantial cohorts, leading to large, lengthy studies which can be difficult to recruit to and lead to incomplete datasets [20]. Using gene expression as our primary endpoint allows us to evaluate inflammatory changes whilst reducing both duration of exposure to study drug and sample size for the study. This not only allows us to evaluate mechanism of action in a more efficient way, but also allows us to address the ethical imperative of reducing the number of participants involved in an invasive study, particularly at this early stage of drug development. Whilst the primary objective of the ARTEMISIA study is to assess the change in epithelial gene signatures, the study will also assess the impact of inhibiting the IL-13, IL-4, IL-6, IFN-γ and TSLP signalling pathways on cellular pathology as a secondary objective.

Performing studies with complex sampling methods at scale increases the risk of logistical challenges and variation in sample collection and quality which may lead to a lack of veracity of the data that is collected. Given the risks and complexity, to perform bronchoscopy on participants at a scale which would allow the data collected to be related directly to clinical outcomes would be resource intensive and difficult to deliver. Identifying a relationship between central and peripheral biomarkers which can then be related to clinical outcomes in a separate large-scale study offers a solution to this problem. Evaluating epithelial gene signatures has allowed us to keep the sample size small, reducing possible site-to-site sampling variability and logistical complexity. By collecting the same peripheral samples in both the ARTEMISIA and AJAX studies, associations between biomarkers in central and peripheral samples will be evaluated, and subsequently related to clinical outcomes, without needing to expose large numbers of participants to the risks associated with invasive sampling.

Randomisation in the ARTEMISIA study will be stratified based on baseline FeNO as a non-invasive approach to enrol participants across the spectrum of T2- and T17-driven airway inflammation. FeNO level has previously been reported to be positively correlated with T2 gene expression signatures and inversely correlated with T17 gene expression in airway epithelial cells [13].

Key barriers to performing studies of this nature include participant acceptability but also feasibility of delivery at the site level. To address these challenges, the study protocol was reviewed and critiqued by a group of asthma patients, as well as a group of research nurses from the UK NIHR Clinical Research Facility Network. The study was also reviewed and subsequently adopted by the NIHR translational research collaboration. By incorporating the perspective of participants and research delivery staff, the authors hope to have created a study design which achieves its objectives but remains acceptable and feasible to deliver from the outset.

There are limitations to our study design. Whilst the sample size has intentionally been kept to a minimum for the reasons set out above, this may limit data interpretation, particularly when attempting to assess the effect of londamocitinib in T2 and non-T2 predominant asthma. ARTEMISIA is a hypothesis-generating study designed to provide insights to inform the future clinical development plans for londamocitinib. Another limitation is that due to the short duration of exposure to study drug and small sample size, meaningful changes in clinical effects are not anticipated. This is mitigated for by collecting the same nasal, blood and urine samples in the much larger AJAX study which is designed to investigate clinical outcome measures and is exposing 320 participants to study drug for 12 weeks.

## Conclusion

There is a large unmet need for new treatments in asthma which target non-T2 inflammatory pathways. ARTEMISIA will evaluate the effect of londamocitinib, a novel JAK-1 inhibitor, on gene expression in the airways of a broad population of uncontrolled, moderate-to-severe asthma with varying degrees of T2 inflammation. ARTEMISIA not only aims to assess the impact of londamocitinib on T2 and non-T2 inflammatory pathways, but also delineate the relationship between the central and peripheral airway, and potentially identify novel biomarkers assessed with minimally invasive sampling methods that can be used to identify those with non-T2 inflammation. Whilst the participants taking part in ARTEMISIA all have asthma, insights gained from this study may inform future work assessing the utility of JAK1 inhibition in other respiratory diseases.

## Data Availability

No datasets were generated or analysed during the current study.

## Abbreviations

ACQ: Asthma Control Questionnaire
ANCOVA: Analysis of covariance
BID: Twice daily
BMI: Body mass index
CAAT: Chronic Airways Assessment Test
Compex Asthma: Composite endpoint for asthma exacerbations
FeNO: Fractional exhaled Nitric Oxide
FEV_1_: Forced expiratory volume in 1 second
GINA: Global Initiative for Asthma
GSVA: Gene set variation analysis
HIV: Human immunodeficiency virus
ICS: Inhaled corticosteroids
IHC: Immunohistochemistry
IFN: Interferon
IL: Interleukin
JAK: Janus kinase
LABA: Long-acting beta agonists
LAMA: Long-acting muscarinic antagonist
LTRA: Leukotriene receptor antagonist
MMRM: Mixed model for repeated measures
PPB: Parts per billion
RNA: Ribonucleic acid
Seq: Sequencing
Singscore: Single-sample scoring
SNP: Single nucleotide polymorphism
STAT: Signal transducer and activator of transcription
T2: Type 2
Th: T-helper
TSLP: Thymic stromal lymphopoietin
UK: United Kingdom
